# A multicentric, 2 × 2 factorial, randomised, open-label trial to evaluate the clinical effectiveness of structured physical activity training and cognitive behavioural therapy versus usual care in heart failure patients: a protocol for the PACT-HF trial

**DOI:** 10.12688/wellcomeopenres.18047.1

**Published:** 2022-08-12

**Keywords:** Factorial trial, heart failure, cardiac rehabilitation, exercise, behaviour therapy, India

## Abstract

**Background:** Heart failure (HF) is a multi-morbid chronic condition, which adversely affects the quality of life of the affected individual. Engaging the patient and their caregivers in self-care is known to reduce mortality, rehospitalisation and improve quality of life among HF patients. The PACT-HF trial will answer whether clinical benefits in terms of mortality and hospitalisation outcomes can be demonstrated by using a pragmatic design to explore the specific effects of physical activity, and cognitive behavioural therapy in HF patients in India.

**Methods:** We will conduct a 2
× 2 factorial, randomized, open-label trial, which aims to see if rehabilitation strategies of structured physical activity training and cognitive behavioural therapy for depression and self-management reduce the risk of repeat hospitalisation and deaths in HF patients in India. Patients will be randomised to (1) physical activity + usual care (2) cognitive behaviour therapy + usual care, (3) physical activity + cognitive behaviour therapy + usual care, and (4) usual care at 1:1:1:1 ratio. Time to mortality will be the primary outcome. A composite of mortality and hospitalisation for HF will be the main secondary outcome. Additional secondary outcomes will include ‘days alive and out of hospital’, cumulative hospitalisation, quality of life, Minnesota Living with Heart Failure questionnaire score, depression score, six minutes walking distance, handgrip strength, and adherence to medicines and lifestyle.  The effects of intervention on the primary outcome will be estimated from Cox proportional hazard models. For the continuous secondary outcome variables, differences between randomised groups will be estimated from linear mixed models or generalised estimating equations (GEE) as appropriate.

**Discussion:** PACT-HF is designed to provide reliable evidence about the balance of benefits and risks conferred by physical activity and cognitive behavioural therapy-based cardiac rehabilitation for those with HF, irrespective of their initial disease severity.

## Introduction

Heart failure (HF) is a multi-morbid chronic condition, which adversely impacts the quality of life of the affected individual
^
1,
2
^. The disease burden attributable to HF in India is increasing and the estimated prevalence ranges from 1.3 million to 4.6 million, with an annual incidence of 0.5–1.8 million
^
3
^. Heart failure requires resource-intensive treatment strategies, which are not immediately available and accessible for most patients in India. The financial burden of HF to the patients and their care givers is huge, and represents 2–3% of the total cost of all medical conditions
^
4
^. The estimated cost of HF treatment, resulting from frequent hospital admissions, multiple-drug therapy, comorbidities and device treatments
^
4
^ in 2012, is approximately $1186 million in India
^
4
^. The HF mortality in India is even worse than common cancers with an estimated 40% surviving past five years
^
5
^.

Besides the resource-intensive medical and medical device therapies, engaging the patient and their caregivers in self-care is known to reduce mortality, rehospitalisation and improve quality of life among HF patients
^
6,
7
^. In general, HF patients need to engage in a number of self-care behaviours like adherence to multiple medications, living a healthy life style (
*e.g.* no smoking or drinking alcohol), monitoring symptoms, identifying and addressing warning signs or symptoms, managing depression or psycho-social distress and other co-morbidities
^
1,
8
^. The ability to participate in and adhere to self-care behaviours becomes more challenging to people as HF symptoms worsen. Decline in physical function and increased psycho-social distress-related symptoms are common in HF patients as the disease worsens
^
8–
10
^. It may further hinder the individual’s capacity for performing self-care and deteriorates the patient condition in a vicious cycle
^
11
^.

Physical activity is an important core component of cardiac rehabilitation (CR)
^
12
^. Timely introduction of structured and graded physical activity based on the severity of HF symptoms is an important component of cardiac rehabilitation (CR) and is associated with improvements in functional capacity, and quality of life
^
13
^. Studies focusing on CR in India are limited. Even though preliminary works suggesting the benefits of exercise-based CR on functional capacity and quality of life exist
^
14
^, a structured physical activity-based programme that is culturally adapted to the Indian settings has not been evaluated for its effectiveness in reducing hospitalisation and mortality of HF patients.

Modification of negative thoughts and behaviours to positive and healthy ones with the help of cognitive behavioural therapy is another strategy to improve self-care in HF patients with symptoms of depression or psycho-social distress
^
15
^. Although cognitive behavioural therapy is demonstrated as a useful strategy in HF patients, the studies were smaller in terms of participants numbers, and with shorter follow-up. Further, the effectiveness of a culturally adapted behavioural therapy in reducing hospitalisation and mortality has not been evaluated in well-designed randomised controlled trials
^
16
^ in Indian settings.

The PACT-HF trial will answer whether clinical benefits in terms of mortality and hospitalisation outcomes can be demonstrated in HF patients by using a pragmatic design to explore the specific effects of physical activity, and cognitive behavioural therapy in HF patients in India.

## Methods

The study protocol conforms to the CONSORT reporting guidelines
^
17
^ and other relevant guidelines
^
18
^.

### Ethical considerations

The study protocol was approved by the institutional ethical committee of SCTIMST (SCT/IEC/1313.9/AUGUST-2021) and all participating centres. The trial is registered in clinical trial registry of India (CTRI) with registration number CTRI/2020/11/028808. Written informed consent will be obtained from all study participants.

### Study design

We will conduct a 2×2 factorial, randomised, and open label trial to evaluate the specific effects of physical activity and behavioural therapy in reducing mortality and hospitalisation in HF patients in India. The patients recruited in the study will be randomly assigned to one of four intervention groups: a control arm (usual care-C), intervention A (physical activity), intervention B (cognitive behaviour therapy), and a combination of intervention A and B (physical activity + cognitive behaviour therapy)
^
19
^. We assumed no interaction between the treatment arms. 

### Study settings

The study will be carried out in six hospital settings with facilities for management of HF in Kerala, India. Medium to large tertiary care referral hospitals in both private and public settings will be selected for the study with representation from the Southern, Central and Northern parts of Kerala, India.

### Study population

Eligible patients with physician-diagnosed HF
^
2
^ will be invited from the selected hospitals for participation in the trial. HF patients with New York Heart Association (NYHA) class I to IV will be invited to participate in the study. Adults over 18 years old, citizens of India, permanent residents of the state of Kerala, who speak Malayalam language and with physician-diagnosed HF will be included in the trial. We will exclude bedridden patients, patients with known psychiatric disorders and under treatment, and those who refuse to provide written informed consent from the trial. Further, we will exclude currently enrolled patients in other formal cardiac rehabilitation programs.

### Screening and enrolment

All invited participants will be informed about the trial procedures and written informed consent will be obtained from each of them. A detailed participant information sheet will be made available in the local language and will be given to each participant. The recruitment of the patients in the study will be conducted from September 2021 to September 2022 in all study centres. All the identified and consenting participants will be screened based on inclusion and exclusion criteria by a dedicated research nurse
^
20
^. A structured study questionnaire will be used for documenting the screening data
^
21
^.

### Intervention and comparator

Intervention A (physical activity and usual care): Participants will be asked to perform physical activity, along with a structured exercise program of moderate intensity for at least 30 minutes, five days a week throughout the study period.

Intervention B (cognitive behaviour therapy and usual care): Participants will receive individual face-to-face behavioural therapy sessions once a month and telephone sessions once every week.

Intervention C (physical activity + cognitive behaviour therapy and usual care): Participants will receive both behaviour therapy intervention and exercise regime.

Comparator: Participants in the usual care arm will continue without any intervention as suggested above.

### Intervention delivery

A dedicated research nurse with experience in managing HF patients and clinical trials will be recruited in each centre to deliver the intervention. A TIDieR check list
^
22
^ will be circulated among investigators to describe the nature of the intervention and the role of the study team in delivering the intervention along with their expertise (
*Extended data*)
^
23,
24
^.

The research nurses identified in each centre will be given training on cognitive behaviour therapy and physical activity under the guidance of experts in the field. A detailed trainers’ manual and lesson plan will be used for training purposes. Training by experts in the field will be given in a full-day face-to-face session. This will be reinforced by online sessions for clarification of queries and through mock sessions. A compendium containing standard operating procedures, study proforma, reference manual and a logbook to record patient details and narratives will be provided and explained to the research nurse at each site.

The exercise regimen will be demonstrated to the patient in the HF clinic under the supervision of the treating cardiologist. Individually tailored, low-intensity exercises of short duration will be offered initially as a strategy to enhance adherence. The intensity of the exercise will be gradually increased based on tolerance as assessed by Borg’s rating of perceived exertion. The patients enrolled in the cognitive behaviour therapy arm will be given direct in-person as well as telephonic sessions over a period of one year. Upon enrolment, participants will receive a manual on behaviour therapy and physical activity and recorded videos of the exercise program.

### The intervention and training modules

**
*Resource module for physical activity*.** The resource module consists of three manuals: The trainer’s manual (English), and the patient’s manual in English and Malayalam versions (native language). The manual will be used to explain the intensity and duration of exercises with the help of visual art forms. A recorded video of exercises specially designed for HF patients with increasing intensity over time will be included as a tool of intervention. 

**
*Resource module for behaviour therapy*.** It consists of three manuals: The trainer’s manual (English), patient’s manual in English version, and patient’s manual Malayalam version (native language). A recorded video of breathing exercises (relaxation technique) for HF patients will be incorporated as part of the relaxation program. The manual will focus on the interaction between physical health and emotional health.

### Structured physical activity intervention

After the randomisation, the structured physical activity intervention group will receive face-to-face group training sessions by the research nurse in the outpatient settings of the respective study sites. All the intervention participants will be advised to participate in the group session. They will be asked to perform all their activities of daily living, regular physical activity (
*e.g.*, walking, gardening, and household work) along with their exercise of choice. Participants will be informed to engage in mild to moderate exercise for at least 30 minutes, five days a week. The exercise component will be demonstrated over 10 sessions and will include a warm-up and a cool-down session. The participants will be requested to increase the duration of the exercise session according to their tolerance. Yoga-based physical activity will be also introduced as part of the intervention. Very simple and specific yogasanas will be demonstrated to HF patients to increase their overall physical activity.

The participants will be instructed to perform each schedule of exercises and will be asked to increase the intensity gradually every month. The type and duration of exercises will change with the intensity of the exercise that they perform. All participants receiving the exercise training will be given a manual developed in Malayalam (native language) with all instructions. Further, a self-assessment checklist will be provided to capture the fidelity to the intervention regime (
*Extended data*)
^
25
^

Participation in the intervention session will be monitored using self-assessment forms. Participants will be asked to bring these self-assessment forms at each follow-up visit. A mobile phone application (containing the app Metronome Beats) will be used by patients to increase the intensity and duration of exercise. The research team will contact participants weekly through telephone and provide input on modifying and tailoring the exercise intensity and duration. 

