### Cognitive behavioural therapy intervention

The cognitive behavioural therapy modules developed for the study will be simple, easy, and understandable such that the intervention can be given even by even a lay person. The behavioural therapy intervention will consist of individual sessions of 30–45 minutes duration, that will be delivered by a trained nurse. The sessions will be given in the outpatient settings of the study sites. We will use a detailed trainer’s manual to explain the sessions to the research nurse. The delivery of the brief behavioural counselling sessions will be based on a structured guidance document. Participants will receive individual face-to-face sessions once a month and telephone sessions once a week for the next 10 months. The cognitive behavioural therapy sessions will generally involve building rapport with patients, understanding patient’s thoughts and belief about HF, assessing their dysfunctional thoughts, teaching them methods to cope with the disease, incorporating positive thoughts, teaching them methods to relax the mind and reviewing the assignments given to each individual patient. At the end of each session, participants will be required to complete the ‘Mood thermometer
^
26
^’ to see how they feel each day and their mood changes throughout the therapy.

All participants receiving the cognitive behavioural therapy interventions will be given a behavioural therapy manual in their native language. This self-help manual will aid in guiding the participants in unsupervised home tasks and assignments based on behavioural therapy. A self-assessment checklist (
*Extended data*)
^
27
^ will be provided and it will help the participants in monitoring their progress and in attaining therapy-related goals during the follow-up periods.

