### Measurements

The socio-demographic details like age, gender, education, occupation will be recording during the patients’ first visit. Aetiology, history and risk factors for the disease will also be recorded at baseline. Furthermore, recent blood investigations done in the three months prior will be also analysed.

Participants will be seen every three months until the end of the three-year follow-up
^
28
^ will help to identify measurement details at different time points. At study visits, depression and anxiety scores will be collected from each participant by using the PHQ9
^
29
^ and GAD-7
^
30
^ questionnaires, respectively. The self- management component will include assessments of participant’s medication adherence, management of weight and diet, and family support as reported by the patient. The medication adherence will be measured using the four-item Morisky Green Levine medication adherence scale
^
31
^. We will use the multimorbidity treatment burden questionnaire (MTBQ)
^
32
^, to measure treatment burden. The study proforma will also assess the medical utilisation, patient satisfaction in quality of care, family support, and diet management.

We will use the Kansas City Cardiomyopathy Questionnaire (KCCQ)
^
33
^ and EQ-5D-5L
^
34
^ to assess quality of life. The KCCQ assess the disease specific quality of life. The EQ-5D-5L provides a simple descriptive profile and a single index value for health status. Standardized and validated instruments will be used for assessing the functional status, severity of disease, and treatment.

The six-minute walk test (6MWT) will be measured using standard settings during their out-patient visits
^
35
^. The 6MWT will be performed indoors, on a flat-surface corridor, which is 30 m long. Before starting the test, the research nurse will record the blood pressure, pulse rate, and oxygen saturation. The patient will be advised to start the test after being instructed on the test procedure. The test will run for six minutes and will follow all the instructions given by the American Thoracic Society
^
36
^. At the end of the test, the distance covered will be documented along with the pulse rate, blood pressure, oxygen saturation and Borg’s rating of perceived exertion and fatigue.

Hand grip strength will be assessed using standard assessment procedures using a dynamometer
^
37

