## Conclusions

The PACT-HF trial will answer whether physical activity-based training and cognitive behavioural therapy, which are part of the core components of cardiac rehabilitation, will be effective in independently improving survival and quality of life of HF patients in India. We will use culturally appropriate, resource-sensitive and context-specific strategies in the management of HF in Indian settings. The PACT-HF model could be adopted in similar health care settings in LMIC in delivering cardiac rehabilitation for HF patients. 

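### Weekly telephone contact is part of all three active arms and is not stated for usual care, so neither main effect can be read as the specific effect of exercise or of cognitive behavioural therapy

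*Protocol article*

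**What the plan says.** All references are to the protocol article.

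- Physical activity (Structured physical activity intervention): "The research team will contact participants weekly through telephone and provide input on modifying and tailoring the exercise intensity and duration". No end date is given for these calls.
- CBT (Cognitive behavioural therapy intervention): "Participants will receive individual face-to-face sessions once a month and telephone sessions once a week for the next 10 months". The Intervention delivery section instead describes in-person and telephone sessions over one year.
- Combination (Intervention and comparator): "Participants will receive both behaviour therapy intervention and exercise regime". Whether this means one weekly call or two is not said.
- Usual care (same section): "Participants in the usual care arm will continue without any intervention as suggested above". Contact that would also cover this arm is the study visit (Measurements: "Participants will be seen every three months until the end of the three-year follow-up") and a telephone follow-up of each patient, mentioned under Data management without frequency or content.

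The Study design section adds: "We assumed no interaction between the treatment arms". The Introduction and Study design sections say that the trial examines the specific effects of the two components. The Conclusions section says that it will show whether they "will be effective in independently improving survival and quality of life of HF patients in India".

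**The concern.** In a 2 × 2 factorial trial, a main effect isolates its own component only if everything else is balanced across the levels of that factor. Here weekly calls occur in both arms with physical activity but in only one of the two arms without it. The same is true for CBT. Contact thus behaves like a third component that is missing only from usual care.

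The Introduction makes such an effect plausible, since it credits engagement in self-care with lower mortality and fewer readmissions. If calls helped and exercise did not, the physical activity main effect would still be favourable, and the planned conclusion would credit exercise. The self-reported outcomes, in an open-label trial, are more exposed to this than mortality.

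**Working it through.** **The plan's own figure.** The Sample size section gives 1632 participants for 80% power, 50% three-year mortality and a 20% relative reduction (50% to 40%), and the Statistical analysis section gives two-sided 5%. For two proportions:

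n = [1.96·√(2·0.45·0.55) + 0.842·√(0.5·0.5 + 0.4·0.6)]² / 0.10² = 388 per group after rounding up, or 408 with continuity correction. Then 4 × 408 = 1632, an exact match. The trial is therefore sized for a comparison of one arm with another, which matters for the fix.

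**Balance of weekly contact, counted from the text.**

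| Factor level | Arms with weekly calls |
|---|---|
| Physical activity: yes | 2 of 2 |
| Physical activity: no | 1 of 2 |
| CBT: yes | 2 of 2 |
| CBT: no | 1 of 2 |

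**Where a contact effect goes.** Let a and b be the specific log hazard ratios and c that of weekly contact. Usual care is 0, physical activity a + c, and CBT b + c.

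*A second call adds nothing.* The combination arm is a + b + c.
- Physical activity main effect: [(a + c) + (a + b + c)]/2 − [0 + (b + c)]/2 = a + c/2. By symmetry, CBT gives b + c/2.
- Interaction: (a + b + c) − (a + c) − (b + c) + 0 = −c.

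*Two calls that add up.* The combination arm is a + b + 2c.
- Main effects: a + c and b + c.
- Interaction: (a + b + 2c) − (a + c) − (b + c) + 0 = 0.

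*Contact has no effect* (c = 0): no bias and no interaction.

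If single arms are compared with usual care instead, physical activity gives a + c and CBT gives b + c under either model.

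**Size.** The documents do not give c, so the contact hazard ratios below are assumptions. Specific effects are set to nil, with 408 per arm and 50% mortality in usual care. Expected events in an arm are 408·(1 − 0.5^HR), and the standard error of a main effect is ½·√(sum of 1/events over the four arms).

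| Assumed contact HR | Main-effect HR, second call adds nothing | Chance of p < 0.05 | Main-effect HR, calls add | Chance of p < 0.05 |
|---|---|---|---|---|
| 0.95 | 0.975 | 6.5% | 0.95 | 11.1% |
| 0.90 | 0.949 | 11.3% | 0.90 | 30.5% |
| 0.85 | 0.922 | 19.9% | 0.85 | 58.9% |
| 0.80 | 0.894 | 32.2% | 0.80 | 83.3% |

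For contact HR 0.90 where a second call adds nothing: exp(½·ln 0.90) = 0.949, and the interaction ratio is 1/0.90 = 1.11. A test would detect that interaction with probability of only 11.3%, so a non-significant interaction test would not be reassuring.

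**Contrasts with calls on both sides.** If a second call adds nothing, or only one is made, combination versus CBT alone is (a + b + c) − (b + c) = a, and combination versus physical activity alone is b. If two calls are made and add up, these become a + c and b + c, and nothing is gained.

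**The case against.** The strongest defence is that this is a pragmatic trial of rehabilitation strategies and that the calls are not generic attention. One set tailors exercise and the other delivers therapy, so they are how each programme works. Each programme including its calls is a valid randomised contrast, and specific or independent might mean only each factor apart from the other. Most of this stands. It supports claiming a programme effect, but not attributing that effect to exercise or CBT themselves. Even the reading of each factor apart from the other is not secured, because both programmes share weekly contact.

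It is also fair that no document shows that telephone contact changes mortality. The size is therefore conditional.

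A reader might infer more than the text supports:

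- *That the no-interaction assumption must fail.* It fails through this route only if contact works and its benefit does not add up in the combination arm. With two additive calls the interaction is zero.
- *That late contact falls wholly on the physical activity factor.* This would need those calls to outlast the CBT calls. Their duration is not stated, the CBT duration is given two ways, and the exercise schedule and intervention checklist are extended data not shown here.
- *That usual care has nothing beyond the three-monthly visits.* The Data management section mentions telephone follow-up of each patient, though it does not show matched weekly contact.
- *That all contact is with a nurse.* For CBT the sessions are ones "that will be delivered by a trained nurse". The physical activity calls are made by the research team.
- *That the analysis is fixed on pooled margins.* The Statistical analysis section does not say so, but contrasts of a single programme with usual care carry the whole of c.

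**Conclusion.** The point holds as a fault of interpretation. From the call schedule alone, contact is unbalanced on both factors. While both sets of calls run, each main effect carries about half of any contact effect if a second call adds nothing, or all of it if calls add. In neither case is it a specific effect, unless contact does nothing. The absence of interaction is an assumption that the schedule leaves unsecured. It is not shown to be false.

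With an assumed contact hazard ratio of 0.90 and no specific effects, each main effect would show 0.95 or 0.90, and would reach significance with probability of about 11% or 30%. These figures rest on the assumed 0.90, proportional hazards, 50% mortality in usual care and an equal contact effect for both kinds of call. The randomised comparison of each programme with its calls, and the sample size of 1632, are unaffected.

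**What to change.** 1. In the Introduction, Study design and Conclusions sections, claim the effect of each programme including its telephone contact, in place of specific or independent effects.
2. Treat the absence of interaction as an assumption to be examined, and report the interaction estimate with its confidence interval.
3. Beside the main effects, report combination versus CBT alone and combination versus physical activity alone.
4. State whether the combination arm receives one weekly call or two. The contrasts in item 3 are matched on calls by design only with one. They also stay matched only while both call schedules run, and only on telephone contact, since CBT also has monthly face-to-face sessions.
5. Reconcile the two stated CBT durations (10 months and one year), and state how long the physical activity calls last.

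This needs wording and two further contrasts on data already being collected. Changing the calls themselves in a trial that began data collection in September 2021 would be another matter and is not asked for.

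The price is a narrower claim and less precision. With similar event numbers per arm (e), the standard error is √(2/e) for a contrast of two arms and ½·√(4/e) = √(1/e) for a main effect, so intervals are about √2 = 1.41 times as wide on the log scale. With 408 per arm, power is about 82% for 50% versus 40%. If the background therapy also lowers mortality by 20%, the contrast is 40% versus 32%: 0.08/√[(0.40·0.60 + 0.32·0.68)/408] = 2.39, and 2.39 − 1.96 = 0.43, so power is about 67%.
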